# Telehealth multicomponent exercise and health education in breast cancer patients undergoing primary treatment: rationale and methodological protocol for a randomized clinical trial (ABRACE: Telehealth)

**DOI:** 10.1186/s13063-022-07015-z

**Published:** 2023-01-19

**Keywords:** Breast neoplasms, Physical exercise, Resistance training, Telehealth, Telemedicine, Telerehabilitation, Mobile health, mHealth, Digital intervention, Fatigue

## Abstract

**Background:**

Current guidelines emphasize cancer patients should increase their physical activity levels, encouraging physical exercise practice as a complementary therapy to mitigate adverse effects during treatment. Telehealth can be a feasible method to improve adherence and interventional support for breast cancer patients, of which most do not meet sufficient physical activity levels after diagnosis. The Adaptations to Breast Cancer and Exercise Using Telehealth (ABRACE: Telehealth) study aims to investigate the effects of a 12-week telehealth multicomponent training program plus a health education program (MTHE), compared to a health education program alone (HE), on physical and psychological outcomes in breast cancer patients undergoing treatment.

**Methods:**

This study is a randomized controlled trial. Women undergoing primary treatment (during or after chemotherapy) for breast cancer (stages I–III) will be randomly assigned to MTHE (twice a week) or HE (once a week). MTHE components are mobility, aerobic, balance, resistance, and flexibility home-based exercises, supervised by video call. The primary study outcome is cancer-related fatigue. The secondary outcomes are quality of life, symptoms of depression and anxiety, physical activity level, cancer-related cognitive impairment, and functional capacity. Other outcomes are adherence to interventions and a follow-up questionnaire evaluating the individual perception in motivation, lifestyle changes, and main barriers to participation. All outcomes will be remotely assessed before and after intervention. Our analysis will follow the intention-to-treat approach and per-protocol criteria, with additional sub-group analysis.

**Discussion:**

To our knowledge, this is the first randomized clinical trial in breast cancer patients using a face-to-face videoconference strategy to supervise physical exercise. Our hypothesis is of superiority for the effects of MTHE on primary and secondary outcomes compared to the effects of only the health education intervention.

**Trial registration:**

Adaptations to Breast Cancer and Exercise Using Telehealth (ABRACE: Telehealth), NCT04641377. Registered on 23 November 2021, https://clinicaltrials.gov/ct2/show/NCT04641377

**Supplementary Information:**

The online version contains supplementary material available at 10.1186/s13063-022-07015-z.

## Background

Cancer is the second leading cause of death worldwide, with breast cancer being the most frequently diagnosed type [50, 57]. Although breast cancer incidence rates are 88% higher in developed countries, the mortality rates are 17% higher in developing countries compared to developed countries [50]. The advancements in early detection methods and more effective treatments have contributed to a higher survival rate in 5 years and a decline in mortality in this population in developed countries [2, 12].

Chemotherapy as part of primary cancer treatment increases the chances of survival [21]. In contrast, there is a need to counteract health issues related to disease and toxicity of treatments, which can lead to short- and long-term side effects in cardiovascular, neuromuscular, and immune systems [27, 30, 53]. Additionally, the cancer treatment can increase cancer-related fatigue, impair quality of life, and negatively affect mental health and patients’ ability to perform daily activities [4, 25, 27].

Physical exercise has been shown as a complementary therapy during breast cancer treatment aiming to mitigate the adverse effects of medication and improve patients’ quality of life [9]. Current exercise guideline for cancer survivors [9] recommends moderate-intensity aerobic training at least 3 times per week, for at least 30 min, in addition to twice-weekly resistance exercise comprising one exercise per major muscle group, 8 to 15 repetitions per set, 2 sets per exercise. Moreover, patients should avoid inactivity and increase physical activity progressively according to their ability and health condition [22]. Despite these recommendations encouraging an active lifestyle, only 11–19% of cancer patients meet sufficient physical activity levels after the diagnosis [6, 52]. Some perceived barriers include the adverse effects of treatment (e.g., fatigue), low motivation, lack of time, lack of access to fitness facilities, and low social support [14]. Also, most oncology patients prefer exercising at home [14, 59]. In addition, training supervision is an advantageous strategy to improve health outcomes, such as quality of life, physical function, anxiety, and depression symptoms, compared with non-supervised exercise in cancer patients [7, 9, 51].

As an alternative methodology, telehealth is an important tool to improve the monitoring and delivering of a physical exercise program for cancer patients, besides being safe and low-cost [5, 48]. Telehealth can be defined as distance-based interventions delivered using information and communication technologies to assess, educate, monitor, and/or guide physical exercises or other health care interventions [5, 45]. However, the efficacy of home-based exercise on fatigue and psychosocial outcomes in breast cancer patients undergoing primary treatment is not entirely established. A meta-analysis including seven unsupervised home-based interventions [55] found no positive effect on cancer-related fatigue in patients ongoing breast cancer treatment. On the other side, a recent meta-analysis study including cancer survivors demonstrated that home-based physical activity interventions induced small improvements in fatigue for up to 9 months [23]. It is important to highlight that the participation rate in these home-based interventions was higher (mean 55.33%) than in previous studies during (41–43% )[11, 54] and after (37%) [26] treatment. Although adherence to exercise is a positive feature in home-based interventions, the heterogeneity among exercise protocols is remarkable regardless of the environment [59]. Previous interventions did not attend principles of training and exercise recommendations as an indication of the quantity and multiples components (i.e., mobility, aerobic, balance, resistance, and flexibility exercises). Also, these studies failed to adequately report exercise prescription variables (i.e., frequency, intensity, time, and type), hindering the protocol application by health professionals and the comparison between studies [15, 39].

Therefore, our study aims to evaluate the effect of telehealth multicomponent training plus a health education program, compared to a health education only, on fatigue, quality of life, anxiety and depression symptoms, and functional capacity in women undergoing primary treatment for breast cancer. The choice of the active comparator group intends to reach the principle of equipoise and partially accounts for research participation effects (Hawthorne effect). Our central hypothesis is of superiority for the effects of multicomponent training plus a health education program group (MTHE) on primary and secondary outcomes compared to the effects of only a health education program (HE).

## Methods

### Protocol registration

The *A*daptations to *Br*e*a*st *C*ancer and *E*xercise Using Telehealth (ABRACE: Telehealth) study is a two-armed randomized controlled trial registered on Clinical Trials (NCT04641377) on November 23, 2020, before the first participant enrolment (i.e., on February 26, 2021). The planned flow diagram of this trial is presented in Fig. 1.

**Fig. 1 Fig1:**
[figure not shown]
The ABRACE: Telehealth trial design

### Study setting and eligibility criteria

This trial will take place in Porto Alegre and Pelotas, cities located in southern Brazil. The research team and the necessary training equipment present in the interventions are from *Universidade Federal do Rio Grande do Sul* and *Universidade Federal de Pelotas*. The protocol study will be conducted following the SPIRIT (Standard Protocol Items: Recommendations for Interventional Trials) statement [10]. Participants will be recruited through advertising on social media, in local newspapers, and at hospitals and oncology clinics in the cities involved in the study. After initial contact with researchers, volunteer will schedule an interview with the one of the researchers. The participants will be inquired about all eligibility criteria by a trained evaluator through a video call, which will be performed individually to ensure the eligibility of the participants. Inclusion criteria for subjects are defined as follows: (1) women living in Porto Alegre or Pelotas; (2) aged 18 years or older; (3) medical diagnosis of breast cancer in stages I-III [3]; (4) volunteers undergoing primary treatment for breast cancer (i.e., adjuvant or neoadjuvant chemotherapy; or radiotherapy or immunotherapy after chemotherapy); (5) physically inactive at least three months prior to eligibility (i.e., women who do not reach current physical activity guidelines of at least 150 min of aerobic and/or muscle-strengthening activities on 2 or more days a week) [8]; and (6) willing to participate in any arm of the study.

Exclusion criteria are considered: (1) inability or unwillingness to give informed consent for participation; (2) absence of internet access or internet-enabled device; (3) presence of serious orthopedic, cardiovascular, or cardiopulmonary conditions that limit physical exercise participation; (4) major psychiatric or cognitive disorders; or (5) were otherwise not cleared by their oncologist.

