### Primary outcome

The primary study outcome is cancer-related fatigue, which will be assessed using the Piper fatigue scale. Cancer-related fatigue was chosen as the primary outcome because it is a widespread side effect caused by chemotherapy, and it is identified among high-priority cancer- and treatment-related toxicities based on its potential to affect cancer care rapidly [28, 38].

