#### Sample size

The sample size estimation was based on the number of patients feasible to collect given our financial resources during the period of the study (concomitant with the COVID-19 pandemic )[29]. We estimate that the total sample will be around 30 participants. Therefore, approximately 15 women will be enrolled in each group.

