#### Assignment of interventions and blinding

After consent, each participant will receive an internal identifier number. After completing the baseline assessments, participants are randomized to either the MTHE or HE. A blinded investigator created a computer-generated randomization sequence, via random function (Excel software), 1:1 ratio, with a block of random sizes that are not disclosed to ensure concealment. The allocation concealment is implemented by researchers in charge of requesting randomization for one of the blind investigators with access to the randomization list ([name], [name]), via email, from the identifier number. A researcher ([name]) allocates individuals in the groups by phone call or WhatsApp message. Randomization requests follow the order in which participants complete the baseline assessments. The allocation date of the participants is recorded in an Excel spreadsheet.

Blinding will be applied for assessors of all primary and secondary outcomes, except physical activity level and cognitive function (the researcher monitoring these two evaluations is not blinded, but both questionnaires are self-administered). Participants are asked to omit their assigned group and not talk about their interventions during the outcome assessments. Due to the nature of the intervention, the study staff supervising training sessions and participants are non-blinding. In unblinding cases, the principal investigator will be notified with the participant ID, date, and reasons for unblinding.

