#### Statistical considerations

Generalized Estimating Equations (GEE) and Bonferroni post hoc tests will be used for comparison between time points (baseline and post-intervention) and groups (MTHE and HE) for both per-protocol and intention-to-treat analyses. The per-protocol analysis (PP) will count all women with training frequency ≥ 70% of intervention sessions (≥ 16 sessions for participants allocated in the exercise program, and ≥ 8 sessions for participants allocated to the education program). For the intention-to-treat analyses, the incomplete data (i.e., missing values) will be estimated using maximum likelihood estimation by the automatic regression imputation method.

Additionally, we plan to carry out subgroup analysis stratifying both groups by clinical characteristics of the tumor (histological type of tumor, tumor staging, and status of hormone receptors) and treatment (chemotherapy and radiotherapy protocols). Considering that withdrawals may occur due to specific harms or other non-anticipated reasons, we will assess whether additional grouping (indicator) should be made due to different missing data patterns. Therefore, we will qualitatively document reasons and details of withdrawals on a case-by-case basis. Continuous variables will be summarized according to intervention groups at baseline, if applicable, and end of trial using arithmetic or geometric means, standard deviations, ranges, and interquartile ranges as appropriate. According to intervention groups, categorical variables at baseline and end of the trial (if applicable) will be summarized as absolute number and proportion of subjects (%). Standardized effect sizes will be calculated by dividing the between-group difference of the post-intervention means by the pooled baseline standard deviation. The significance level established for all analyses will be *p* < 0.05, and all statistical procedures will be analyzed and processed using the SPSS version 22.0 software.

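### Women on and past chemotherapy are pooled without stratification or a phase term in the stated fatigue model, which costs precision and leaves the estimate exposed to chance imbalance in phase

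*Protocol article*

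**What the plan says.** Criterion 4 in the protocol article's section Study setting and eligibility criteria admits "volunteers undergoing primary treatment for breast cancer (i.e., adjuvant or neoadjuvant chemotherapy; or radiotherapy or immunotherapy after chemotherapy". The abstract's Methods paragraph describes the same mix, so both phases enter one randomised comparison.

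Under Assignment of interventions and blinding, allocation follows one computer-generated sequence, "1:1 ratio, with a block of random sizes that are not disclosed to ensure concealment", issued in the order in which women finish baseline. No stratification factor is named.

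Statistical considerations gives a GEE that compares baseline with post-intervention and MTHE with HE. No covariate is named. Treatment appears there only among the planned subgroup factors, after the tumour characteristics, as "treatment (chemotherapy and radiotherapy protocols".

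The section Primary outcome justifies the choice of fatigue partly because "it is a widespread side effect caused by chemotherapy". Sample size states "We estimate that the total sample will be around 30 participants", that is, "approximately 15 women will be enrolled in each group".

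**The concern.** By the protocol's own reasoning, whether a woman is receiving chemotherapy bears on her fatigue. Over 12 weeks, women in treatment and women past it may well follow different courses. The group-by-time contrast removes a phase difference in baseline fatigue level, but not a difference in course. The planned standardised effect size uses post-intervention means, so it does not remove even the difference in level.

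Two things are at stake. The spread between phases stays in the residual variance and widens the interval on the primary outcome. And with about 15 women per arm, the split of phases between arms can be uneven enough to move the estimate noticeably in the one trial that is run. Random block sizes keep the arms equal in number. They balance phase only so far as phase drifts with enrolment time.

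**Working it through.** **The plan's own figure.** The total of about 30 cannot be reproduced: "The sample size estimation was based on the number of patients feasible to collect given our financial resources", with no effect size, SD or power. For scale, 15 per arm at two-sided 5% detects (1.960 + 0.842) × √(2/15) = 1.02 SD with 80% power (about 1.06 SD with the t distribution). The level comes from "The significance level established for all analyses will be *p* < 0.05"; that it is two-sided is assumed.

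**Inputs from the protocol.** 30 women, 15 per arm, 1:1, no stratification; Piper scale 0 to 10.

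**Assumptions, since the protocol gives no values.** 15 of 30 women on chemotherapy at entry (9 to 18 also tried). Difference between phases in mean 12-week fatigue change D = 1, 2 or 3 points. Within-phase SD of change s = 2 points. So D/s = 0.5, 1.0 or 1.5.

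1. *Chance imbalance (hypergeometric).* There are C(30,15) = 155,117,520 ways to split the women.
   - Gap of 1 woman (8 v 7): 2 × 6435² / 155,117,520 = 0.534.
   - Gap of 3 (9 v 6): 2 × 5005² / 155,117,520 = 0.323.
   - P(gap ≥ 3) = 1 − 0.534 = 0.466. P(gap ≥ 5) = 0.466 − 0.323 = 0.143.
   - With 12 or 18 women on chemotherapy, P(gap ≥ 4) = 0.264. With 9, P(gap ≥ 5) = 0.109.

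2. *Shift given the split.* Shift = (gap/15) × D. For 10 v 5: (5/15) × 1, 2, 3 = 0.33, 0.67, 1.00 points.

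3. *Variance when phase is left out.* Ratio = 1 + 0.25 × D²/s² = 1.06, 1.25, 1.56.

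4. *Error rates.* The type I error at a 10 v 5 split is a normal approximation with a t critical value. The power columns come from 20,000 simulated trials per setting, using a linear model with and without phase, averaged over all splits. The true effect is 0.8 SD (0.8 × 2 = 1.6 points).

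| D (D/s) | Shift, 10 v 5 | Variance ratio | Type I error, 10 v 5 | Power without phase | Power with phase |
|---|---|---|---|---|---|
| 1 (0.5) | 0.33 | 1.06 | 5.5% | 54% | 55% |
| 2 (1.0) | 0.67 | 1.25 | 8.9% | 46% | 54% |
| 3 (1.5) | 1.00 | 1.56 | 12.7% | 39% | 54% |

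5. *Averaged over all splits,* type I error is about 5% in every setting, with or without phase. At the most even split (8 v 7) it is below 5% (3.6%, 2.4% and 1.3% for the three values of D), which offsets the excess at uneven splits.

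6. *Direction matters.* At D/s = 1.0 and 10 v 5, power for the 0.8 SD effect is 80% if the imbalance favours MTHE and 16% if it goes against it. It is 47% with no shift.

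**The case against.** Unstratified randomisation is valid, and ordinary standard errors already allow for chance imbalance. A reader might infer that pooling the phases biases the trial or invalidates its test. Step 5 shows otherwise. What remains is a shift conditional on the split that occurs, and lost precision. The same could be said of any prognostic factor in a trial of 30, though phase is the one that the protocol ties to its primary outcome.

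The larger shifts are also tail cases. Under the same assumptions the likeliest gap is a single woman (53%). The mean absolute gap is about 2.3 women, or (2.3/15) × 2 = 0.3 points at D = 2. Even the 0.67-point shift is below one standard error of the effect, 2 × √(2/15) = 0.73 before phase variance is added. This stands, and it limits the size of the point.

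Three further readings go beyond the text:

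- *The GEE excludes covariates.* The article prints no model formula, and an analysis plan that is not shown could name covariates. The point is therefore an improvement to the model as stated.
- *The protocol says that fatigue rises on chemotherapy and falls afterwards.* It gives no time course. Women past chemotherapy are still on radiotherapy or immunotherapy, and the Background says that cancer treatment in general can increase fatigue. D is an assumption.
- *Treatment is ignored.* Subgroups by chemotherapy and radiotherapy protocols are planned. They are not defined by phase at entry, do not adjust the main comparison, and would leave few women per cell.

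**Conclusion.** The point holds as a matter of precision and of exposure to chance imbalance. The stated design and model pool two treatment phases that, on the protocol's own account of fatigue, are likely to differ on the primary outcome. Its size depends on an assumed phase share, phase effect and SD. At a phase effect of about 0.5 SD the loss is small (power 54% against 55%). At 1.0 SD it is material (46% against 54%), and at 1.5 SD more so (39% against 54%). In a trial that has 80% power only for effects of about 1 SD, that precision is worth recovering.

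**What to change.** Add one sentence to Statistical considerations: *the primary fatigue GEE will include treatment phase at baseline (on chemotherapy or after chemotherapy) and its interaction with time, for all women.* Fix this before outcomes are compared by arm, so that it cannot be read as a response to an imbalance already seen.

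Take phase from the eligibility screening, where criterion 4 requires it to be established. The section Sociodemographic and clinical characteristics lists the treatment protocols used, and does not name phase at entry.

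The cost is one or two degrees of freedom. A binary term is only a partial remedy, because it puts a woman starting chemotherapy together with one about to finish it.

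Running separate block lists for the two phases is optional. Trial status plans recruitment from March 2021 to March 2023, and the article appeared on 19 January 2023. On that schedule about two of some 24 months remained, so stratifying the last allocations would help few women. The covariate serves all of them.

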### Interventions

A detailed description of both interventions is provided below:

### Multicomponent training and health education group (MTHE)

The MTHE will be performed twice a week over 12 weeks, on pre-established and non-consecutive days. The sessions will be held by video call on Google Meet platform (approximately 60 min of duration) in small groups (maximum of three patients) and are supervised by physical education students or professionals previously trained to carry out the intervention. The first session of the training program will be performed individually (i.e., 1:1 supervision ratio) to ensure adequate orientation. All equipment and materials will be delivered to participants at the beginning of the intervention (i.e., two pairs of 2- and 4-kg dumbbells and one exercise mattress). The exercises within a training session will be ordered as follows: warm-up (joint mobilization and aerobic stimulus), balance exercise, resistance exercise, and stretching of the main muscles used during the training session. The training periodization used throughout the 12 weeks can be seen in Table 1.

**Table 1 Tab1:** Training periodization and exercises used throughout the 12 weeks intervention in the MTHE group

Volume	Weeks 1–4	Weeks 5–8	Weeks 9–12
Joint mobilization: 2 sets × 10 repetitions each	Joint mobilization: Stiff and shoulder front raise	Joint mobilization: Stiff and shoulder front raise	Joint mobilization: Stiff and shoulder front raise
Aerobic stimulus: 2–3 sets × 20 s	Aerobic (2 sets): Skipping	Aerobic (2 sets): Adapted Jumping jacks	Aerobic (3 sets): Skipping (session A); Jumping jacks (session B)
Balance exercises: 2 sets × 20 s	Balance: Single leg stance (Right leg + Left leg)	Balance: Imaginary line walking	Balance: Airplane Pose (Right leg + Left leg)
Resistance exercises: 2–3 sets × 10–15 repetitions 10 exercises	Resistance (2 sets × 10–12 repetitions, 5–6 OMNI) exercises (a):	Resistance (2–3* sets × 10–12 repetitions, 6–7 OMNI) exercises (b):	Resistance (2–3* sets × 12–15 repetitions, 7–8 OMNI) exercises:
Static stretching exercises and health education once a week	Dumbbell floor press, Pelvic lift, One-arm dumbbell row, Chair squat, Lateral raises, Split squat Biceps curl, Crunch, Lying triceps extension Isometric crunch	Dumbbell fly*, Unilateral pelvic lift, One arm wide grip dumbbell row*, Dynamic plus isometric squat, Front raise, Lunge*, Hammer curl, Dynamic plus isometric lying triceps extension, Isometric reverse crunch, Bird dog	First session of the week: exercises (a) (Dumbbell floor press*, One arm row*, Split squat*) Second session of the week: exercises (b) (Dumbbell fly*, One arm wide grip dumbbell row*, Lunge*)

In the resistance exercises labeled with “*” 3 sets are performed; in the remaining exercises, 2 sets. In exercises labeled as “dynamic plus isometric” 10 dynamic repetitions plus 5 to 10 s of isometric contraction of the same exercise are performed per set; in exercises labeled as isometric only, each set will last 10 to 15 s

The warm-up is comprised of joint mobilization in low intensity (i.e., using a stick or broomstick as load) and the aerobic stimulus through skipping exercise and adapted jumping jacks (restricting shoulder abduction until 90°, to prevent discomforts related to surgery or treatment). The warm-up will last for approximately 7 min.

In the main part of the session, balance exercises will be performed through single-leg stance, progressing to walking in an imaginary line, and airplane poses in subsequent mesocycles. Thereafter, ten resistance exercises will be performed in pairs alternated by body segment (upper limbs–lower limbs). The intensity will be controlled through an individual’s Rating of Perceived Exertion (RPE), ranging from 5 to 8 on an OMNI scale of 0 to 10 in which zero is no effort (rest), and 10 is a maximal effort [36]. The investigators will use the following question after each exercise: “how hard do you feel your muscles are working?”. Dumbbells will be used for resistance exercises, except for core, pelvic lifting, and split squat exercises. Exercises will change every 4 weeks. The exercises performed in each mesocycle are presented in Additional file 0^1^. The exercises will be performed with a 20:20 cadence (i.e., 2 s of eccentric phase, no pause during the transition, and 2 s of concentric phase). When the intended RPE is not achieved, the cadence will be increased to 40:20, and/or the external load will be increased. The last strategy to achieve the desired RPE is to perform 2 s of isometric contraction on the most challenging angle of the exercise movement in each repetition. The exercises will be alternated by segments, with 30-s rest between exercises and 90-s rest between sets for the same exercise. Due to fluctuations in exercise tolerance, capacity, and self-efficacy during treatment, a flexible prescription allowing patients to auto-regulate the session’s intensity according to their condition in each session will be ensured [22]. Instructional videos of exercises will be sent to participants of the MTHE before the video call session. In the last mesocycle, the exercises are a combination of those performed in the first 8 weeks. The main part of the training session will last from 38 to 50 min.

The cool-down phase will last 5–10 min, during which participants will perform static stretching exercises on major muscle groups (pectoralis major, latissimus dorsi, hamstring, adductor, and glutes) for one set of 20 s each. Additionally, in the second training session of each week, after stretching exercises, the supervisor will address one health education topic, based on the same contents planned for the health education group, but more briefly, lasting 15–20 min. All participants will be instructed to report difficulties and limitations, and training variables (i.e., RPE, load, cadence, and total volume) or any exercise adaptation are registered.

